# **14. Monitoring**

|  | Y | N | Comments |
| --- | --- | --- | --- |
| Does the research involve greater than minimal risk (i.e., the harms or discomforts described are beyond those ordinarily encountered in daily life or during the performance of routine physical or psychological tests)? |  |  |  |

# **15. Data Analysis**

**Internal/External Validity**

To avoid study bias in the collection of data, several measures have been implemented to enhance both internal and external validity. To address internal validity, random sampling techniques have been employed to ensure that a diverse group of participants is selected (who still meet eligibility criteria), reducing selection bias. Additionally, questions are designed to be neutral and clear, minimizing response bias.

To improve external validity, the survey is distributed to the study’s target population, ensuring the results are relevant to that population. Since participants are not anonymous, efforts are made to ensure confidentiality, reducing the risk of social desirability bias and promoting more honest responses.

**Data Analysis Techniques**

Power Analysis: Biochemically verified 7-day point prevalence abstinence from cigarettes at the end of the 12- week Switch Phase by study arm (ONP, NRT) is the primary outcome of the study and was chosen because it is a critical outcome to inform public health interventions and potential FDA regulations of ONPs. It is also stringent statistically, requiring a sample size that will provide sufficient statistical power to examine the other study outcomes. Although we will not biochemically confirm use of NRT or ONP, biochemical verification of abstinence from cigarettes combined with self-reported use of NRT or ONP is indicative of complete switching. To derive our NRT arm abstinence estimate of 13% we used our prior trial that investigated the effects of NRT sampling on cessation outcomes.^70^ Crucially, this trial included a sample of rural participants; in this rural subsample, the cessation rate was 13%.^70^ We derived our ONP arm estimate of 23% based on our preliminary data. As the goal of that study was not switching, we believe this estimate to be conservative. Assuming 80% retention at the end of the 12-week Switch Phase, a total sample of 800 participants (400 per arm), will provide greater than 95% power to detect a difference in smoking abstinence between the NRT and ONP arms for a two-sided, α=0.05 level chi-squared test. Further assuming 70% retention at the end of the 14-week Observation Phase, a sample of 700 (350 per arm) will provide over 90% power to detect a significant difference between the ONP and NRT arms.

Data Analytic Plan: Statistical analyses will be performed using SAS 9.4. P-values less than 0.05 will be considered statistically significant. Baseline demographics and smoker characteristics will be summarized by arm (ONP and NRT), as appropriate. Continuous variables will be presented as mean ± standard deviation and compared between the arms with t-tests. Categorical variables will be presented as frequencies and proportions and compared with chi-squared tests. Balance of all covariates according to randomization will be confirmed prior to conducting the below analyses. Any imbalanced covariates will be controlled for in regression models.

Aim 1: The examination of differential levels of (H1a) switching, (H1b) abstinence from cigarettes, and (H1c) cigarettes smoked per day, between the ONP and NRT study arms at the end of the 12-week Switch Phase will be the focus of Aim 1. Hypotheses 1a-b: Complete switching rates and abstinence from cigarettes will be compared between arms using logistic regression analysis, adjusting for baseline variables as needed. In an exploratory analysis, we will also evaluate whether sex modifies the associations between study group and the switching and abstinence outcomes using product interaction terms (see Section C.11). Hypothesis 1c: If needed, we will apply a normalizing transformation to the number of cigarettes smoked per day (e.g., taking the logarithm) before proceeding with the analysis as a means of removing the effects of potential outliers. We will compare cigarettes smoked per day between the two arms using linear regression analysis. The model will adjust for cigarettes smoked per day at baseline and other baseline variables if they are imbalanced.

Aim 2: The focus of Aim 2 is the examination of (H2a) product appeal and (H2b) cigarette craving and nicotine withdrawal at the end of the Switch Phase and (H2c) among complete switchers, change in cigarette dependence from baseline to the end of the Switch Phase between the study arms. Hypothesis 2a: We will examine differences in product appeal between the ONP and NRT arms at the end of the Switch Phase with linear regression models. These models will be adjusted for potential confounders including baseline variables such as age, gender, number of cigarettes smoked per day, and/or randomization stratification factors as necessary; normalizing transformations will be employed if needed. Hypothesis 2b: Similar to hypothesis 1a, the analysis of cigarette craving and withdrawal symptoms will be evaluated with linear regression models adjusting for appropriate confounders. Hypothesis 2c: Among participants who completely switched to their assigned study product, change in nicotine dependence from baseline will be compared between smoking abstainers in the ONP and NRT arms using linear regression analysis, adjusting for baseline nicotine dependence and other variables as outlined in Hypothesis 2a.

Aim 3: Aim 3 will examine differences between the ONP and NRT arms in (H3a) abstinence from cigarettes, (H3b) number of days the study products are used, and (H3c) purchase and continued use of the study products during the 14-week Observation Phase. Hypothesis 3a: The analysis of abstinence from cigarettes at the end of the Observation Phase will mirror that of hypothesis 1b and will be evaluated with a logistic regression model. Hypothesis 3b: Linear regression analysis will be used to compare the number of days the products are used during the Observation Phase between the ONP and NRT arms; a normalizing transformation will be employed if needed and appropriate baseline characteristics will be adjusted for. Hypothesis 3c: The continued purchase and use of either ONP or NRT after during the 14-week Observation Phase will be compared between the arms with logistic regression analysis, adjusting for all appropriate confounders. Missing Data: In the event of missing data, we will contact participants immediately. If a participant drops out, we will attempt to gather follow-up information by calling and trying to reach the participant through other provided contact information. However, if a participant refuses to be contacted or loses contact with the investigators, we will censor data at point of loss. Two statistical approaches will be used to handle missing data. First, we will use inverse probability weighting with propensity scores. This is a two-step procedure in which we first model the probability of missingness as a function of baseline covariates and previous outcomes. Next, the inverse of the resulting predicted probabilities (from the logistic regression model) will serve as weights in our proposed model of the response. We will compare these results to a more conservative intent-to-treat approach as a final step.

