Follow-up survey among adult smokers who participated in an acute ONP use clinical trial. After completing the trial described above, several participants contacted us to thank us for introducing them to ONPs and anecdotally shared that they cut down on smoking using ONPs. In response, we developed a 6-month follow-up survey to ask all participants about their tobacco use and perceptions of ONPs. Although cessation was never a goal of the acute use study, 23% of participants who were daily smokers at baseline reported that they now smoke “rarely” or “not at all.” In open-ended responses, participants who reduced or quit smoking noted that ONPs were “stronger” and more enjoyable than they expected and that they were “a helpful tool” for quitting smoking. Conclusion: Without a planned switching outcome, a substantial proportion of rural Appalachian participants switched from cigarettes to ONPs on their own following short-term exposure to ONPs.

Large, nationwide, remote trials of alternative nicotine products. We have significant experience conducting large, nationwide, trials of alternative nicotine products. Co-I [name] has led 5 state- or nationwide remote trials of NRT (Ns=616, 849),^61,62^ one nationwide, remote trial of snus (N=1236),^63,64^ and one remote trial of electronic cigarettes (R01CA210625). MPI [name] is a Co-I on the electronic cigarette trial. MPI [name] ([name] is a Co-I) also recently completed accrual for a remote, randomized trial (U01DA045537) comparing electronic cigarettes vs. NRT on smoking outcomes among recent tobacco Quitline treatment failures from two states (Oklahoma and South Carolina). This study recruited 350 participants within 18 months with 80% retention. Each of these studies demonstrates our ability to recruit large numbers of smokers, distribute products efficiently via mail, and complete follow-up assessments with strong retention.

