Studies collecting data via smartphone and biomarkers remotely. Our team has considerable remote data collection experience using smartphones to complete follow-up assessments (11 studies, including one among rural Appalachian smokers) and Bedfont’s iCO device to collect exhaled carbon monoxide (CO) remotely (4 studies; e.g., U01DA045537). Importantly, these studies have helped us improve upon our participant instructions and troubleshooting procedures to maximize adherence. For example, we significantly improved adherence to the iCO device from 61% to 87% by simply modeling its use via video calls/conference (e.g., Zoom, FaceTime), in addition to written and pictorial instructions.

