**Number of Participants**

We expect up to 1,000 participants to enroll in this study. Each subject must meet I/E criteria.

Assuming 80% retention at the end of the 12-week Switch Phase, a total sample of 800 participants (400 per arm), will provide greater than 95% power to detect a difference in smoking abstinence between the NRT and ONP arms for a two-sided, a=0.05 level chi-squared test. Further assuming 70% retention at the end of the 14-week Observation Phase, a sample of 700 (350 per arm) will provide over 90% power to detect significant difference between the ONP and NRT arms.

All study activities will take place remotely using participants’ study devices.

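### The 23% ONP abstinence rate behind the stated power appears to come from a pilot figure that also counts people who still smoke rarely, so the power claims are unsupported and 23% is not shown to be conservative

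*Protocol*

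**What the plan says.** Protocol section 15 (Data Analysis Techniques, Power Analysis) names the primary outcome as "Biochemically verified 7-day point prevalence abstinence from cigarettes at the end of the 12- week Switch Phase by study arm (ONP, NRT"). Section 3 (Obtain exhaled iCO) sets the CO criterion for abstinence at 6 ppm or less.

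For the control arm, section 15 states: "To derive our NRT arm abstinence estimate of 13% we used our prior trial that investigated the effects of NRT sampling on cessation outcomes", and adds that "in this rural subsample, the cessation rate was 13" percent. For the ONP arm it states: "We derived our ONP arm estimate of 23% based on our preliminary data". It defends that figure as follows: "As the goal of that study was not switching, we believe this estimate to be conservative".

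It assumes 80% retention at the end of the Switch Phase (400 per arm) and 70% at the end of the Observation Phase (350 per arm). Section 5 (Number of Participants) repeats that the first of these "will provide greater than 95% power to detect a difference in smoking abstinence between the NRT and ONP arms", and claims over 90% for the second. No abstinence rates are given specifically for the Observation Phase.

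The preliminary data are in section 1 (Preliminary Research). After an acute-use crossover study of 30 smokers, a survey at 6 months found that "23% of participants who were daily smokers at baseline reported that they now smoke “rarely” or “not at all". The same paragraph says that cessation was not a goal of that study, and it describes those who changed as having reduced or quit.

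**The concern.** The planning rate and the endpoint measure different things. The endpoint needs seven days without cigarettes and a confirming CO reading. The pilot figure is a self-report with no CO check described, and it adds people who still smoke occasionally to people who have stopped. Someone who smokes rarely may pass a 7-day test or may fail it; the pilot category does not distinguish the two. The NRT rate, by contrast, is described as a cessation rate, so the looser definition sits only in the arm expected to do better.

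The protocol's reason for calling 23% conservative is that the pilot did not aim at switching. That concerns how strong the intervention was and does not address the looser outcome definition.

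This is the only sample-size justification for the primary outcome. Section 1 also says in advance what a finding of no difference would mean: smokers should be directed to NRT or other methods. The weight of such a conclusion depends on credible power.

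**Working it through.** **1. Tracing the 23%.** Section 15 does not cite its source by name. Section 1 contains one 23% among the preliminary studies, and it comes from a study described, as in section 15, as having no cessation or switching aim. The link is an inference, but no other figure fits.

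**2. Reproducing the plan's power.** Inputs from section 15: NRT p₁ = 0.13, ONP p₂ = 0.23, two-sided α = 0.05, chi-squared test, n = 400 or 350 per arm. With p̄ = (p₁ + p₂)/2:

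- s₀ = √[2p̄(1 − p̄)/n] (standard error under the null)
- s₁ = √[p₁(1 − p₁)/n + p₂(1 − p₂)/n] (standard error under the alternative)
- power = Φ[(p₂ − p₁ − 1.96·s₀)/s₁]

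At n = 400: s₀ = √(2 × 0.18 × 0.82/400) = 0.02717 and s₁ = √[(0.1131 + 0.1771)/400] = 0.02694. Then (0.10 − 0.05324)/0.02694 = 1.736, and power = **95.9%**.

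At n = 350: s₀ = 0.02904 and s₁ = 0.02879. Then (0.10 − 0.05692)/0.02879 = 1.496, and power = **93.3%**.

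The unpooled version gives 96.0% and 93.5%; a continuity correction gives 95.0% and 91.9%. Both stated figures reproduce.

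**3. Dependence on the ONP rate.** The same formula with NRT fixed at 13%. Every ONP rate other than 23% is an assumption, because the protocol does not split the pilot's two answer categories.

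| ONP rate | Power, 400/arm | Power, 350/arm |
|---|---|---|
| 23% | 95.9% | 93.3% |
| 22% | 91.9% | 88.1% |
| 21% | 85.5% | 80.6% |
| 20% | 76.1% | 70.4% |
| 19% | 63.9% | 58.2% |
| 18% | 49.8% | 44.7% |

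**4. Rates the claims require.** Solving for p₂ against 13%:

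| Power | 400/arm | 350/arm |
|---|---|---|
| 80% | 20.4% | 20.9% |
| 90% | 21.7% | 22.3% |
| 95% | 22.7% | not needed for the claim |

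The claim of more than 95% therefore has a margin of about 0.3 percentage points (23 − 22.7), and the claim of over 90% about 0.7 points (23 − 22.3).

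**5. Scale of one answer in the pilot (illustration only).** The denominator of the 23% is not given. If all 30 participants counted, 7/30 = 23.3% and 6/30 = 20.0%. One respondent who smoked rarely and would have failed the 7-day test would then move the rate from the first row of the table in step 3 to about the 20% row. The exact 95% interval for 7/30 is 9.9% to 42.3%, which includes the 13% assumed for NRT.

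**The case against.** The strongest reply is the protocol's own. Pilot participants used the product in an acute-use study, were not asked to switch, and were surveyed at 6 months. This trial offers two weeks of sampling, a switch date and 12 weeks of free product. True ONP abstinence could well exceed the pilot's. This stands, and it is why the documents do not show that the power is too low. It does not establish that 23% is conservative, because no data are offered to show that the stronger intervention outweighs the looser outcome.

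A reader might be tempted by four stronger readings, none of which the documents support:

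- *That the power is miscalculated.* It is not; both figures reproduce. The question concerns an input.
- *That 13% is too low because controls here receive combination NRT.* The protocol does not describe the NRT form, duration, time point or verification behind the 13%, so the direction of any error is unknown and any replacement rate would be invented.
- *That incomplete CO testing shrinks the sample further.* The protocol reports that "we significantly improved adherence to the iCO device from 61% to 87% by simply modeling its use via video calls/conference". A participant who reports smoking is a failure without any CO reading, so that percentage cannot be applied to everyone retained. The assumed retention may also already reflect completed assessments.
- *That the Observation Phase claim holds only if 13% and 23% persist after free product ends.* It does not: at 350 per arm, 10% versus 19% gives 92.4%. The gap is that the assumed rates are not stated.

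**Conclusion.** The concern holds as an unsupported planning input. The 23% appears to measure a broader, unverified outcome than the endpoint being powered, and it bounds self-reported abstinence in the pilot from above. The description of it as conservative is not justified.

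The stated power is correct for 13% versus 23%, but it has almost no room: the two claims fail below about 22.7% and 22.3% respectively, and at an assumed 20% power would be 76% and 70%. No single corrected figure can be given, because the share of the 23% that had stopped entirely is not reported. A reader should not conclude that the trial is underpowered: at 400 per arm it has 80% power for 20.4% against 13%, and the true ONP rate may be higher than the pilot's.

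The conclusion rests on the inferred link between sections 15 and 1, on NRT at 13%, and on the protocol's retention assumptions.

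**What to change.** Keep N=1,000 and revise the wording in section 5 (Number of Participants) and section 15 (Power Analysis):

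- Remove the statement that the ONP estimate is conservative.
- If the pilot records allow, report how many respondents answered that they did not smoke at all, with the denominator, and base the ONP rate on that count.
- If they do not, replace the single power figures with detectable ONP rates against 13%. At 400 per arm: 20.4%, 21.7% and 22.7% for 80%, 90% and 95% power. At 350 per arm: 20.9% and 22.3% for 80% and 90% power.
- State the abstinence rates in both arms that underlie the Observation Phase figure.

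The change is to wording only: no extra participants and no change to endpoint or analysis. The cost is that the stated power will look less favourable than it does now.

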# **2. Objectives**

**Primary Objectives and Outcome Measures**

This study will be carried out in a group of adults (≥21 years old) cigarette smokers (n=1000) from rural Appalachian regions of the United States according to the following aims.

**Aim 1:** Evaluate short-term changes in cigarette smoking patterns, including switching, abstinence from cigarettes, and frequency of smoking between ONPs and NRT. At the conclusion of the Switch Phase, the highest rates of (H1a) complete switching (cigarette abstinence + study product use) and (H1b) abstinence from cigarettes will occur in the ONP group. H1c: ONP participants will smoke the fewest cigarettes per day.

**Aim 2:** Compare product appeal, craving, withdrawal relief, and perceived cigarette dependence between ONPs and NRT. Participants randomized to ONPs will report (H2a) greater product appeal and (H2b) greater reduction in craving and withdrawal symptoms than participants randomized to NRT. H2c: Among complete switchers, ONP participants will report greater reductions in cigarette dependence than NRT participants.

**Aim 3:** Examine sustained changes in tobacco use behaviors, including abstinence from cigarettes, purchase of ONPs/NRT, and continued use of ONPs/NRT. During the Observation Phase, ONP participants will (H3a) have higher rates of abstinence from cigarettes, (H3b) use their study product for a greater number of days, and (H3c) be more likely to purchase their study product than participants in the NRT group. With stubbornly high rates of smoking—and consequently lung and oral cancers—existing approaches have been inadequate and cannot be the sole means to reduce smoking in rural Appalachia. We propose to evaluate the effectiveness of a potentially reduced harm tobacco product, ONPs, which has significant appeal to rural Appalachian smokers. With expertise conducting remote, large-scale switching trials, our team is uniquely suited to conduct this investigation. This urgently needed and innovative study will be critical for public health officials, regulators, and healthcare providers working to reduce cancer disparities in rural Appalachia.

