At the conclusion of the Orientation Call, participants will be emailed or texted a link to the baseline questionnaire ***(Survey Message, Baseline Survey).*** The baseline survey will ask which flavors the participant would like to sample. Participants will be asked about both NRT and ONPs since randomization will not have occurred yet. Participants will be asked to complete the baseline survey in 3 days. Study staff will call, email or text (any combination based on participant preferences) participants up to 10 times over the course of two weeks to remind them to complete the survey. ***(Survey Reminder).***

Following completion of the baseline survey, participants will be randomized to one of two arms for a period of 14 weeks (the Sampling and Switch Phases): 1) ONPs or 2) combination NRT. Randomization will occur using a stratified block-randomization procedure with small, random sized-blocks. Randomization will be stratified by self-reported cigarette dependence, sex, and ONP use history (ever vs. never). We will use FTND<5 vs FTND>=5 for the cigarette dependence portion of the randomization.

Study Kits/Products: Following randomization, participants will be mailed their study kits. Study kits will be tailored to each study group. Study kits will include a Welcome Card ***(Welcome Card),*** welcome/thank-you letter ***(Welcome Letter),*** copy of the consent form, ***(NRT / ONP Fact Sheet)****,* study product guidelines ***(NRT / ONP Guidelines)****,* study product troubleshooting tips ***(NRT / ONP Tips),*** nicotine overdose fact sheet ***(Nicotine Overdose Fact Sheet)*,** participant roadmap outlining their involvement in the study ***(Participant Roadmap),*** individual carbon monoxide (iCO) device and instructions ***(iCOquit Instructions),*** pregnancy test for those who can become pregnant, and study product to sample. The study kit will also include the participant’s ClinCard, and information on how to use the ClinCard ***(ClinCard Info Sheet, ClinCard FAQs)*** and information about the referral program ***(Referral Letter, Referral Flyer).***

The ONP Group will receive three flavors based on what they chose on the baseline survey. They will receive 3 mg and 6 mg concentrations in each flavor.

The NRT group will receive 14 mg and 21 mg patches, and they will receive one to three flavors of lozenges based on what they chose on the baseline survey. They will receive 2 mg and 4 mg concentrations in each flavor.

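### The primary abstinence model takes its covariates from observed baseline imbalance, so the three stratification factors are in practice left out and the odds ratio estimated depends on chance

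*Protocol*

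**What the plan says.** **Design.** In section 3 (Baseline Phase) the protocol states: "Randomization will be stratified by self-reported cigarette dependence, sex, and ONP use history (ever vs. never"). The dependence cut is FTND below 5 versus 5 or more. The factors are listed again under Randomization, Blinding, and Unblinding.

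**Primary outcome.** Section 15 names it as "Biochemically verified 7-day point prevalence abstinence from cigarettes at the end of the 12- week Switch Phase". This is H1b.

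**Covariate rule.** The Data Analytic Plan in section 15 tests baseline variables between arms, requires balance to be confirmed before the outcome analyses, and adds: "Any imbalanced covariates will be controlled for in regression models".

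**Models.**
- H1a and H1b: logistic regression, "adjusting for baseline variables as needed". No covariate is named.
- H3a: mirrors H1b.
- H1c: baseline cigarettes per day is always included; other variables only if imbalanced.
- H2a: age, gender, cigarettes per day and the stratification factors are listed as optional candidates.
- H2b: "the analysis of cigarette craving and withdrawal symptoms will be evaluated with linear regression models adjusting for appropriate confounders". No baseline score is named.
- H2c: baseline dependence is always included.

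**The concern.** For H1a, H1b and H3a, the only meaning that the protocol gives to adjusting as needed is the imbalance rule. That rule has three weaknesses.

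1. It selects on the wrong property. A covariate helps an analysis when it predicts the outcome, and a difference between arms at baseline does not show that.
2. It works against the design. Variables important enough to stratify on are the ones that stratified blocks keep balanced, so the rule passes over them.
3. It leaves the estimand open. An odds ratio adjusted for a prognostic covariate is conditional, and it differs from the marginal one even under perfect balance. If chance picks the covariates, chance also picks which odds ratio is reported.

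H2b has a related gap. Section 2 hypothesises "H2b) greater reduction in craving and withdrawal symptoms than participants randomized to NRT", which is a change from baseline, yet its model does not name the baseline score. The cross-reference there is to H1a, a logistic model without a covariate list, so it supplies none.

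**Working it through.** **1. Reproduce the stated power.** Inputs from section 15: "NRT arm abstinence estimate of 13"%, an ONP estimate of 23%, 400 per arm at week 12 and 350 per arm at the end of the Observation Phase, "for a two-sided, α=0.05 level chi-squared test". With mean rate 0.18, power = Φ{(0.10 − 1.96·√(2·0.18·0.82/n)) / √((0.13·0.87 + 0.23·0.77)/n)}.

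- n = 400: (0.10 − 1.96 × 0.02717)/0.02694 = 1.736, power 95.9% (stated: above 95%).
- n = 350: (0.10 − 1.96 × 0.02904)/0.02880 = 1.496, power 93.3% (stated: above 90%).

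Both figures hold, and the sample size is not in question.

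**2. How often chance changes the model.** The protocol gives neither a number of baseline variables nor a threshold for imbalance. Assume k independent variables and p < 0.05, the general significance level in section 15. The chance of at least one apparent imbalance under sound randomisation is 1 − 0.95^k:

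| k | 3 | 5 | 10 | 15 | 20 |
|---|---|---|---|---|---|
| chance | 14% | 23% | 40% | 54% | 64% |

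**3. What the rule does at the planned size.** Simulation with 800 participants, blocks of 2 and 4 within the 8 strata, and 13% vs 23%. Assumptions: factor prevalences 50/50/25%; ten further baseline covariates, one of them with log-odds ratio 0 or 0.5; 4,000 null and 3,000 alternative trials per scenario. Monte Carlo standard error is about 0.3 to 0.4 points. Each cell gives unadjusted / imbalance rule / three factors fixed, in %.

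| Log-odds ratio per stratification factor | Other covariate | Type I error | Power |
|---|---|---|---|
| 0.5 | 0 | 4.98 / 4.92 / 5.35 | 95.90 / 95.73 / 96.13 |
| 0.5 | 0.5 | 4.35 / 4.18 / 4.68 | 96.10 / 96.03 / 96.33 |
| 1.0 | 0 | 3.82 / 3.92 / 4.58 | 96.37 / 96.37 / 97.03 |
| 1.0 | 0.5 | 4.35 / 4.48 / 5.18 | 96.70 / 96.77 / 97.17 |

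- The rule added some covariate in 39 to 42% of trials and a stratification factor in 0%.
- Fixing the three factors gained 0.2 to 0.7 power points over no adjustment.
- Type I error under the rule was 3.9 to 4.9%, so it is not inflated. The clearest conservatism (3.8 to 3.9%, unadjusted and under the rule) appeared when the factors were strongly prognostic.

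**4. Which odds ratio.** The planned rates give a marginal odds ratio of (0.23/0.77)/(0.13/0.87) = 2.00. In a separate simulation at 13% vs 23%, with assumed log-odds effects of 1.0, 0.4 and 0.5 for the factors and 0.5 per SD of cigarettes per day, adjustment moved the average estimate from about 2.01 to 2.13 and its log-odds standard error from 0.191 to 0.200. Power went from 95.7% unadjusted to 96.1% with the three factors and 96.4% with cigarettes per day as well.

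**The case against.** The case on the other side is substantial, and much of it limits the size of the point.

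- **Other models.** A reader might infer that every covariate in every model enters only through imbalance. The text does not support that: H1c and H2c each fix their baseline value, and H2a lists candidates, including the stratification factors.
- **Error rates and power.** A reader might infer that choosing covariates from data inflates type I error or costs the trial real power. Neither follows. The balance check uses baseline variables and precedes the outcome models, the simulated error rate is not above 5%, and the power at stake is under 1 point. Conservatism is not uniform either: the separate simulation gave 5.3% unadjusted type I error, with the mean standard error matching the empirical spread (0.212 vs 0.211).
- **Imbalance may not be pure chance.** Randomisation precedes the iCO and pregnancy checks, participants who fail them leave the intent-to-treat sample after arm-specific kits have been mailed, the trial is open-label, and 20% loss is assumed by week 12. Looking at balance in the analysed sample therefore has a purpose. Prespecified prognostic covariates answer that concern better than a significance test, however. The simulation did not model such losses.
- **Detail for an analysis plan.** Adjusting as needed does not bar the stratification factors, and a full covariate list often sits in an SAP. That stands for H2b, where the baseline score is not excluded and the protocol does not say that craving and withdrawal are measured at baseline. It does not dispose of the main point: the protocol states a selection rule, and an SAP that fixed the covariates would have to replace it.

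**Conclusion.** The point holds for H1b, and for H1a and H3a, which are built like it. The stated rule lets chance choose the covariates, almost never selects the factors used to stratify, and so leaves unfixed which odds ratio is estimated. This is a mismatch between design and analysis and an avoidable looseness in the primary model. It does not threaten the trial's validity or its sample size.

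The size is small: under about 1 power point at 13% vs 23% with 400 per arm, at most slight conservatism, and no type I error inflation. These figures rest on assumed factor prevalences and covariate effects, and on p < 0.05 as the imbalance threshold, which the protocol does not state. The H2b gap is a secondary matter of wording. The change is worth making because it is cheap and settles the primary model in advance.

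**What to change.** Before any outcome data are seen, replace the covariate rule in section 15 with one paragraph stating that:

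- the H1a, H1b and H3a logistic models include arm, FTND stratum, sex, ONP ever-use and baseline cigarettes per day, whatever the observed balance;
- the three stratification factors enter the other models as well, with H1c and H2c keeping the baseline values that they already fix;
- H2b includes the baseline craving or withdrawal score, where it is collected;
- the baseline table is descriptive, without significance tests, and imbalance does not drive covariate choice.

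The cost is one paragraph and no change to sample size or procedures. The stratification factors are known at randomisation, and H1c already needs baseline cigarettes per day. The one small downside is that the adjusted odds ratio is conditional, while the power statement rests on an unadjusted comparison of proportions. Label the odds ratio as conditional, or also report a standardised risk difference.
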